#### Secondary Outcome Measures

Secondary outcome measures include viral load, analyzed categorically (suppressed vs not) at the 12-month outcome, using <400 copies/mL as suppressed (consistent with recent work analyzing chart-extracted viral load data from the same clinics in Khayelitsha). CD4 is analyzed continuously at the 12-month outcome. In addition, HIV medication adherence and depression scores over time are examined as secondary outcomes using the 4-, 8-, and 12-month assessment time points.

The ultimate data analytic approach will depend on the distribution of the data. We anticipate that we will use generalized linear models), which are estimated using generalized estimating equations with robust standard error estimates to account for repeated measures of the outcome. For the primary outcomes, we will examine adherence scores longitudinally using the Wisepill data and Hamilton scores using the 2 time points (baseline to 4 months) comparing the 2 study arms. For outcomes assessed at the 4 major assessments (ie, baseline and 4, 8, and 12 months), we will use repeated measures analyses. For 12-month viral load, we will test the proportion of those who are suppressed using Fisher exact test. If continuous viral load data are analyzed, we will make log transformations and examine viral load using repeated measures. To reduce bias, the intention-to-treat principle is utilized, where individuals are analyzed according to the condition they were randomized, regardless of their fidelity to that condition.

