**Conclusions:**

Results of this study will inform whether an existing intervention (CBT-AD) can be effectively administered in LMIC by nurses with training and ongoing supervision. This will present unique opportunities to further explore the scale-up of a behavioral intervention to enhance ART adherence among persons living with HIV with major depression in a high-prevalence setting, to move toward achieving The Joint United Nations Programme on HIV/AIDS 90-90-90 goals.

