CBT is an effective treatment for MDD, with a strong evidence base [24]. In the context of MDD in chronic disease care, there are data to support its use to improve both MDD and adherence [25-27]. There is growing evidence that CBT for both adherence and MDD (ie, CBT-AD) might be effective in LMIC and in South Africa in particular. In an open case series of 14 sessions of CBT for depression in HIV clinics in Cape Town [28], 6 participants experienced a marked reduction in depressive symptoms during the course of treatment. This study established initial feasibility and acceptability for CBT for depression applied to PLWH in South Africa with a CBT psychologist as the interventionist. A further pilot study of 14 participants evaluated a shortened, nurse-delivered, integrated CBT-AD intervention adapted to the South African context [29]. Although improvements in adherence and mood were robust, there were challenges in provider fidelity to the intervention, which required intensive training and supervision. Further work to develop an effective, yet scalable, CBT-AD intervention is, therefore, necessary. In addition to the key issues of adherence and remission of depression, the issue of task-sharing of the intervention to nonpsychologists needs to be explored.

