### Interventions

#### Intervention Training

Before starting the study, nurse interventionists completed a weeklong training in the intervention that was conducted by the US and South African investigators. The South African investigators then provided further training until the nurses were deemed competent to begin administering the intervention. Since the nurses started administering the intervention to participants, the project director and the other South Africa–based clinical psychologist provide weekly supervision for an hour with support from the US investigators when needed. Moreover, 1 therapy session from each interventionist is orally translated by the RAs during the week it occurred and is listened to by the clinical psychologists in preparation for supervision. Approximately yearly, interventionists have booster training with the US and South African investigators to prevent drift and enhance fidelity and competence to the protocol.

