#### Standard of Care—Enhanced Treatment as Usual

The clinic nurse provides feedback to the participant and to their clinic doctor (via a letter) about their MDD diagnosis. In addition, all participants undergo standard of care adherence counseling in the clinic, which may include several sessions with a clinic counselor. The letter specifically states that they are not restricted in terms of referral or treatment of MDD for their patient with respect to antidepressant medications or other interventions available.

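### CBT-AD participants are nested within nurse interventionists and ETAU participants are not, but the stated analysis and power inputs allow only for within-participant correlation; if nurses differ, the planned intervals are too narrow for a conclusion about delivery by nurses in general

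*Protocol article*

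**What the plan says.** All references are to the protocol article.

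- **Analysis.** Secondary Outcome Measures, under Data Analysis, also sets out the models for the primary outcomes. It anticipates generalized linear models estimated by "generalized estimating equations with robust standard error estimates to account for repeated measures of the outcome". The choice is left open on one ground: "The ultimate data analytic approach will depend on the distribution of the data". For 12-month viral load, "we will test the proportion of those who are suppressed using Fisher exact test".
- **Power.** Sample Size Considerations lists the inputs: 160 randomized, 20% attrition, 5% type I error and a correlation of 0.5 between observations on the same subject. No correlation between participants of the same nurse appears.
- **Delivery of CBT-AD.** Intervention Training: "Before starting the study, nurse interventionists completed a weeklong training in the intervention". For weekly supervision, "1 therapy session from each interventionist is orally translated by the RAs during the week it occurred". The number of interventionists is not stated.
- **Delivery of ETAU.** Under Standard of Care: "The clinic nurse provides feedback to the participant and to their clinic doctor (via a letter) about their MDD diagnosis". Usual clinic adherence counseling is given as well. No CBT therapist is involved.
- **Target of the conclusion.** The Abstract says that the results will show "whether an existing intervention (CBT-AD) can be effectively administered in LMIC by nurses with training and ongoing supervision". The Discussion presents nurses as a provider group well placed for scale-up.

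**The concern.** In a therapist-delivered arm, participants who share a therapist may have correlated outcomes. Here that can happen only in CBT-AD, which makes the design partially nested. Robust standard errors that cluster on the participant deal with repeated measures on one person. They do not pick up correlation between different participants of the same nurse, and stratifying randomization by site does not do so either. The Fisher test for viral suppression has no nurse term.

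The article does more than stay silent. It names the correlation that the error structure is meant to handle and the correlation used for power, and both are within participant. The one stated ground for changing the approach, the distribution of the data, would not bring in a nurse term.

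What is at stake is how far the result reaches. If one or two nurses achieve much better results than the others, an interval that ignores this will look more precise about nurse delivery in general than the data allow. This applies to both primary outcomes, HAM-D and Wisepill adherence.

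**Working it through.** **Inputs from the article:** 160 randomized, 20% attrition, 5% type I error, a medium effect on depression.

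**Assumptions, because the article gives no figure:** 1:1 allocation (80 per arm, so 80 × 0.8 = 64 evaluable); two-sided test; medium effect d = 0.5; k = 2 to 8 nurses with equal caseloads m = 64/k; ICC of 0.01 to 0.05 in CBT-AD only; equal total variance in both arms.

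**Step 1: the plan's own power figure.** Power = Φ(d/√(2/n) − 1.96).
- n = 80: 0.5/0.158 = 3.162, and Φ(1.202) = 88.5%. This agrees with the stated figure of almost 90%.
- n = 64: 0.5/0.177 = 2.828, and Φ(0.868) = 80.7%. The stated figure is 84%. That gap is a separate matter; 80.7% is the baseline below.

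Neither calculation contains a nurse component.

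**Step 2: add nesting in one arm.**
- Design effect in CBT-AD: D = 1 + (m − 1) × ICC
- Ratio of true to planned standard error: R = √((1 + D)/2)
- Actual two-sided error at nominal 5%: 2 × (1 − Φ(1.96/R))
- Power with the correct standard error: Φ(2.828/R − 1.96)

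Worked case, k = 2 and ICC 0.05: m = 32; D = 1 + 31 × 0.05 = 2.55; R = √1.775 = 1.33; error = 2 × (1 − Φ(1.47)) = 14.1%; power = Φ(0.163) = 57%.

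| Nurses k | Caseload m | ICC | D | SE factor R | Actual error | Power, d = 0.5 |
|---|---|---|---|---|---|---|
| 2 | 32 | 0.01 | 1.31 | 1.08 | 6.8% | 75% |
| 2 | 32 | 0.05 | 2.55 | 1.33 | 14.1% | 57% |
| 4 | 16 | 0.01 | 1.15 | 1.04 | 5.9% | 78% |
| 4 | 16 | 0.05 | 1.75 | 1.17 | 9.5% | 67% |
| 8 | 8 | 0.01 | 1.07 | 1.02 | 5.4% | 79% |
| 8 | 8 | 0.05 | 1.35 | 1.08 | 7.1% | 74% |

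At ICC = 0, D = 1 and R = 1: error stays at 5% and power at 80.7%.

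**Step 3: sensitivity to the setup.** With full retention (80 per arm) caseloads are larger: k = 2 and ICC 0.05 gives R = 1.41 and an error of 16.3%. The 64-per-arm figures are used because the plan itself assumes 20% attrition. The normal reference is lenient when nurses are few, since the between-nurse variance then has very few degrees of freedom.

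**The case against.** The strongest reply is that this is an omission from a condensed article. The analysis wording is provisional, and nothing in it excludes a nurse term in an analysis plan that is not shown. That stands as a reason for moderation: a nurse analysis may exist or could easily be added. It does not remove the point, because the article states which correlation the analysis and the power calculation handle, while its conclusion reaches further.

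A reader might infer that the article itself expects its nurses to differ. It does not say so. The Background reports of the pilot that "there were challenges in provider fidelity to the intervention, which required intensive training and supervision", but this is about fidelity overall, not differences between nurses. The variable success mentioned in the Discussion describes earlier studies. The trial also standardizes delivery through a shared flip-book, training to competence, weekly supervision, session recording and a fidelity checklist. These measures may make the ICC small; they do not put what remains into the standard error.

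A reader might also infer that the intervals are too narrow as a matter of fact, or that the false-positive rate is inflated for any reading of the trial. Neither follows. Both need an ICC above 0, which the article does not give. Even then the inflation concerns inference beyond the nurses involved; for the effect with these nurses, the planned standard error is defensible.

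Three smaller points stand. That the nurse group is small is only an inference from two sites and the supervision routine. The nurse interventionists also assess both arms at baseline, though before randomization, so this creates no therapist level in ETAU. The article does not say that each participant sees a single nurse, and with 2 or 3 nurses a between-nurse variance is barely estimable.

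**Conclusion.** The concern holds conditionally. The design is partially nested, and neither the stated error structure nor the power inputs contain a between-nurse component. If the ICC is above 0, the planned intervals are too narrow for a conclusion about delivery by nurses as a group. The size depends on two quantities that the article does not give. Over 2 to 8 nurses and an ICC of 0.01 to 0.05, with 64 evaluable per arm, it runs from trivial (standard error up 2%, error 5.4%) to substantial (standard error up 33%, error about 14%, power down from 80.7% to 57%). This warrants an added sensitivity analysis and care with the wording of the conclusion, not replacement of the primary analysis.

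**What to change.** 1. Keep the planned GEE analysis as primary.
2. Record the treating nurse for each CBT-AD participant, with a rule for anyone seen by more than one nurse or by none. Report the number of nurses and their caseloads.
3. Add a sensitivity analysis for HAM-D and adherence. If there are enough nurses to estimate the variance, fit a partially nested model (nurse random effect in the CBT-AD arm only) with small-sample degrees of freedom. Otherwise show nurse-specific results and tabulate the primary result over assumed ICCs of 0.01 to 0.05.
4. If that analysis does not support generalization, or the variance cannot be estimated, limit the conclusion to the nurses who took part.

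The cost is one recorded variable and one extra model or table. No trial procedure for participants changes. The downside is a wider interval in the sensitivity analysis, possibly much wider with only 2 or 3 nurses; for that reason the tabulated alternative and the limit on the conclusion should be written down in advance.

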#### Randomization

Approximately 1 month after the initial baseline assessment, participants return for their randomization visit. At this visit, participants are randomly assigned to either CBT-AD or ETAU. Randomization is determined by a computer-generated chart, using the Research Electronic Data Capture (REDCap) randomization module [31]. Study staff enter stratification information (specifically, antidepressant use and site) and click randomize. Antidepressant use is confirmed by paper medical record review. Once the condition has been assigned in REDCap, this field is locked and cannot be changed.

As the study team sends a letter to HIV providers documenting the participants’ depression, regardless of study arm, participants are given the opportunity to start using antidepressant medication outside of the study if they are not already using them. Therefore, at the randomization visit, we stratify randomization by whether or not the participant is taking an antidepressant (2 levels). We are also stratifying by which study site the participant is seen at (2 levels). Note our Data Safety and Monitoring Board (DSMB) reviews baseline data annually for adequacy of randomization.

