#### Secondary Outcomes: HIV Viral Load and CD4 Cell Count

Absolute CD4 cell count and number of HIV viral copies per milli liter of blood are extracted from the participants’ medical record at baseline (to assess the first-line treatment failure inclusion criteria) and at 12-month follow-up. This allows for a calculation of the proportion of patients with virologic suppression. Participants who do not have viral load test results within 1 month of the baseline assessment or 4-, 8-, and 12-month follow-up undergo a blood draw for assay using the COBAS AmpliPrep/TaqMan HIV-1 test (range: 20-10,000,000 copies/mL) [50].

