#### Medications

During baseline assessment, participants will provide information regarding all of their medications (psychiatric, HIV, and other). When completing assessments at every study visit thereafter, patients are asked to report any changes to their medication regimen. These changes are recorded on adherence questionnaires and cross-checked with clinic chart review. Any initiation or changes to antidepressant medications are tracked across all participants and will be used as covariates in analyses.

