#### Sample Size Considerations

The study is powered to detect differences in the depression outcome as well as virologic suppression, and accordingly, a sample size of 160 randomized participants is appropriate. Using repeated measurements with a medium effect, we will have almost 90% power to detect a 10% difference in depression with complete retention at randomization, and assuming 20% attrition, we will have 84% power to detect a difference. On the basis of our earlier efficacy trial that was completed when this study was being designed, for those who entered the study with detectable viral load (in this study, all participants entering will have detectable virus), there was a 20% difference in the proportion of those who had undetectable virus at 12-month follow-up: 40% of those in the control condition compared with 60% of those in the experimental condition [27]. On the basis of these effect sizes, for this study, with a sample size of 160, we are powered to detect differences in the secondary binary outcome, virologic suppression, as follows: we will have >90% power to detect at least a 25% difference and >80% power to detect at least a 20% difference in the proportion of those with detectable viral load. These calculations assume a 20% attrition rate that occurs during the active treatment phase of the study, that the proportion of subjects with viral suppression in the usual care comparison condition is 0.4, that the type I error rate is 5%, and that the correlation between observations on the same subject is 0.5.

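### The 12-month viral suppression test is an unadjusted Fisher exact test: it ignores the randomization strata and baseline viral load and runs well below its nominal 5% level

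*Protocol article*

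**What the plan says.** Under Secondary Outcome Measures the article defines suppression as fewer than 400 copies/mL and fixes the analysis of 12-month viral load: "we will test the proportion of those who are suppressed using Fisher exact test". No strata or covariates are named for it. The same section leaves the overall approach open to the distribution of the data and expects generalized linear models for repeated outcomes. The only alternative it offers for viral load is a repeated-measures analysis of log values, if continuous data are analyzed.

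Four other places bear on this choice:

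- **Randomization**, on antidepressant use: "we stratify randomization by whether or not the participant is taking an antidepressant (2 levels"). Study site is a second two-level factor, so there are four strata.
- **Secondary Outcomes: HIV Viral Load and CD4 Cell Count.** Baseline viral load comes from the medical record. "Participants who do not have viral load test results within 1 month of the baseline assessment", or of a follow-up visit, have blood drawn.
- **Medications.** "Any initiation or changes to antidepressant medications are tracked across all participants and will be used as covariates in analyses".
- **Sample Size Considerations.** Suppression is one of the two outcomes used to justify 160 participants: "we will have >90% power to detect at least a 25% difference and >80% power to detect at least a 20% difference". The stated assumptions are 20% attrition, a control suppression rate of 0.4, 5% type I error and a within-subject correlation of 0.5.

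**The concern.** A single two-by-two table discards information that the trial has already collected: the two factors chosen for stratification, and the baseline value of the outcome itself. It also cannot carry the antidepressant covariate that the Medications section promises for analyses.

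Fisher's test usually rejects less often than its nominal level, so power is lost even before covariates are considered. Sparse cells would be a reason to accept that, but there are none here. At 64 per arm and 40% suppression, the expected counts are 64 × 0.4 = 25.6 suppressed and 38.4 not suppressed.

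At stake is the chance of detecting a real effect on the biological outcome for which the study says it is powered.

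**Working it through.** **Inputs.** From Sample Size Considerations: 160 randomized, 20% attrition, control rate 0.40, differences of 20 and 25 points (0.60 and 0.65), type I error 5%, correlation 0.5. Assumed because not stated: 1:1 allocation and a two-sided test. Analyzed per arm: 80 × 0.8 = 64.

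**Step 1. The plan's own power figures.** The normal approximation is

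power = Φ{ [ |p2 − p1|·√n − 1.96·√(2·p̄·(1 − p̄)) ] / √( p1(1 − p1) + p2(1 − p2) ) }, with p̄ = (p1 + p2)/2.

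- One 12-month comparison, 40% versus 60%, n = 64: (1.600 − 1.386)/0.693 = 0.309, so power is 62.1%.
- 40% versus 65%: (2.000 − 1.384)/0.684 = 0.901, so power is 81.6%.

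Neither reaches the claim of more than 80% and more than 90%. The claim is met, or nearly met, only if the 0.5 correlation is used in a repeated-measures calculation. That replaces n with n / [(1 + (m − 1)·0.5)/m] for m observations per person, and m is not stated.

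| m | factor | effective n per arm | 40% vs 60% | 40% vs 65% |
|---|---|---|---|---|
| 1 | 1.000 | 64 | 62.1% | 81.6% |
| 3 | 0.667 | 96 | 79.6% | 94.0% |
| 4 | 0.625 | 102.4 | 82.1% | 95.3% |

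The power statement therefore matches a different analysis from the one planned.

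**Step 2. The planned test, by exact enumeration.** For each test, power = Σ over a, b from 0 to 64 of Bin(a; 64, p1) × Bin(b; 64, p2) × 1[p-value(a, b) ≤ 0.05]. Type I error is the same sum with p1 = p2.

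| Test, 64 per arm | Size at 40% | Size at 50% | Power 40% vs 60% | Power 40% vs 65% |
|---|---|---|---|---|
| Fisher exact | 3.5% | 3.0% | 53.9% | 75.6% |
| Fisher, mid-p | 4.6% | 4.2% | 59.6% | 79.7% |
| Pearson chi-square | 5.4% | 4.5% | 60.5% | 80.6% |

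The cost of conservatism against Pearson is 60.5 − 53.9 = 6.6 points and 80.6 − 75.6 = 5.0 points. The mid-p row shows that most of this is recoverable with size still below 5% at these two rates. With no attrition (80 per arm), 40% versus 60% gives 65.8% for Fisher and 71.5% for Pearson.

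**Step 3. Using the strata and baseline viral load, by simulation.** There were 4,000 trials per setting, with arms balanced within four strata of equal size and marginal rates held at the target values. The odds ratio per SD of log viral load ran from 1.0 to 2.7, and that for each stratum factor from 1.0 to 1.8. The documents give none of these, so they are assumptions. The Monte Carlo standard error is about √(0.63 × 0.37/4000) = 0.8 points.

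| Analysis, 64 per arm | 40% vs 60% | 40% vs 65% |
|---|---|---|
| Fisher exact | 53–55% | 74–76% |
| Cochran-Mantel-Haenszel, four strata | 61–63% | 80–82% |
| Logistic, strata only | 62–64% | 81–83% |
| Logistic, strata and baseline log viral load | 63–71% | 82–89% |

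A second simulation of 40% versus 60% assumed 30% antidepressant use and log-odds of 0, 0.5 or 0.8 per covariate, with 8,000 trials per scenario. It gave 61–65% for Cochran-Mantel-Haenszel (size 4.8–5.2%), 63–71% for a logistic score test with strata and viral load (size 5.2–5.6%), and 53–54% for Fisher.

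**Step 4. Where the gain comes from.** Moving from Fisher to an unadjusted chi-square yields 5 to 7 points. The strata add about 0 to 2 more. Anything beyond that comes from baseline viral load and depends on how prognostic it is. Within the first simulation the full gain over Fisher is about 9 to 18 points for 40% versus 60%.

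**The case against.** The strongest reply is that Fisher's test is valid, simple and prespecified, that the outcome is secondary, and that choosing it is a matter of taste between accepted methods. It guarantees size control, whereas the adjusted score test ran at 5.2–5.6%, so a little of that test's advantage comes from slight anti-conservatism. The strata contribute little. The viral-load gain rests on assumed prognostic strength, and entry above 400 copies/mL truncates that covariate. The article also foresees model-based analysis and antidepressant covariates in general terms, and a condensed article may leave adjusted estimates and confidence intervals to the SAP. Finally, the larger fault may be that the power statement and the planned test describe different analyses.

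Much of this stands. There is no bias, the upper end of the adjusted range is conditional on assumptions, and the lack of a stated effect estimate is not counted here as an error. The power mismatch is real, and a change of test does not cure it.

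The point itself survives. The article names a specific test for this endpoint, and its general remarks do not replace it. The 5 to 7 points lost to conservatism depend on no prognostic assumption. Size control does not require Fisher: Cochran-Mantel-Haenszel held 4.8–5.2% and the mid-p version stayed below 5% at both rates examined.

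**Conclusion.** The concern holds. The planned test for 12-month suppression ignores both stratification factors and the baseline viral load, and works at a true level of about 3.0–3.5%. With 64 per arm it has 53.9% power for a 20-point difference and 75.6% for a 25-point difference. The certain loss against an uncorrected chi-square is 5 to 7 points. Against a model with strata and baseline viral load, the loss for the 20-point difference is about 9 to 18 points under the covariate strengths assumed. All figures assume 1:1 allocation, two-sided 5% and analysis of the 64 per arm who remain.

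This is an efficiency fault in a secondary outcome, worth correcting because the remedy is nearly free. It does not rescue the power claim: the best adjusted figure for the 20-point difference is 71%, still short of 80%.

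**What to change.** Replace Fisher's exact test with a logistic regression of 12-month suppression on arm, site, antidepressant use as recorded at randomization, and baseline log10 viral load. Report the standardized (marginal) risk difference with its 95% CI. If a single test is preferred, use Cochran-Mantel-Haenszel over the four randomization strata. Keep Fisher for sparse tables only.

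Restate the suppression power for the analysis chosen, and reconcile Sample Size Considerations, which uses a within-subject correlation, with the single 12-month comparison in Secondary Outcome Measures.

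The cost is a change of SAP wording, made before outcomes by arm are seen. All covariates are already collected, and no participant, visit or measurement is added. The price is a model in place of one two-by-two table, and a size that may sit slightly above 5% instead of well below it.
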